## Abstract

**Background:**

There is a dearth of evidence regarding the impact of urban regeneration projects on public health, particularly the nature and degree to which urban regeneration impacts upon health-related behaviour change. Natural experiment methodology enables comprehensive large-scale evaluations of such interventions. The Connswater Community Greenway in Belfast is a major urban regeneration project involving the development of a 9 km linear park, including the provision of new cycle paths and walkways. In addition to the environmental improvements, this complex intervention involves a number of programmes to promote physical activity in the regenerated area. The project affords a unique opportunity to investigate the public health impact of urban regeneration.

**Methods/Design:**

The evaluation framework was informed by the socio-ecological model and guided by the RE-AIM Framework. Key components include: (1) a quasi-experimental before-and-after survey of the Greenway population (repeated cross-sectional design), in tandem with data from a parallel Northern Ireland-wide survey for comparison; (2) an assessment of changes in the local built environment and of walkability using geographic information systems; (3) semi-structured interviews with a purposive sample of survey respondents, and a range of community stakeholders, before and after the regeneration project; and (4) a cost-effectiveness analysis. The primary outcome is change in proportion of individuals identified as being regularly physically active, according to the current UK recommendations. The RE-AIM Framework will be used to make an overall assessment of the impact of the Greenway on the physical activity behaviour of local residents.

**Discussion:**

The Connswater Community Greenway provides a significant opportunity to achieve long-term, population level behaviour change. We argue that urban regeneration may be conceptualised meaningfully as a complex intervention comprising multiple components with the potential, individually and interactively, to affect the behaviour of a diverse population. The development and implementation of our comprehensive evaluation framework reflects this complexity and illuminates an approach to the empirical, rigorous evaluation of urban regeneration. More specifically, this study will add to the much needed evidence-base about the impact of urban regeneration on public health as well as having important implications for the development of natural experiment methodology.

## Background

Most people in high income countries lead inactive lives, fuelling the rise in non-communicable diseases [1]. Physical inactivity has been classified as the fourth leading cause of death worldwide [2]. The potential of the built environment to influence population levels of physical activity was recognised by the World Health Organization [3], and subsequently in the UK Foresight report [4]. However much of the evidence on the relationship between factors such as the design of local neighbourhoods and the provision of opportunities for physical activity has come from cross-sectional studies [5]. The UK Foresight report highlighted the need for evidence of the effectiveness of environmental interventions to help to sustain behaviour changes [4].

A review of gaps in the evidence for physical activity promotion highlighted a need for socio-ecological studies of community interventions [6]. A systematic review of walking to promote physical activity further emphasised the need to study the effects of larger scale community interventions [7]. The UK National Institute for Health and Care Excellence (NICE) review of physical activity interventions prioritised research on the evaluation of effectiveness of environmental interventions on physical activity, especially those including a contemporaneous comparison group [5]. Therefore, there is a gap in the evidence investigating the public health impact of community-wide, environmental change interventions.

Given the scale, it is impossible for researchers to implement built environment interventions and therefore the use of natural experiments has often been the only option to evaluate the impacts of such interventions on health and wellbeing. Natural experiments are interventions that are not under the control of researchers, but often employ observational methods to understand the effects, compared to a control or comparison group [8]. The method enables researchers to evaluate the effectiveness of ‘real world’ public health interventions in the absence of randomised controlled trials [9]. The MRC guidelines for natural experiments recommended the specification of *a priori* hypotheses, clear definitions of target populations, explicit sampling criteria and the use of valid and reliable measures of outcomes [8].

### Aim and objectives

The aim of this study is to determine the impact of a systems-wide community intervention to promote physical activity in the context of a major inner city urban regeneration project.

Specific objectives include evaluating:

(i) The impact of a suite of community-based interventions to promote physical activity;

(ii) The role of the local built environment, and of individual, community and organisational networks in sustaining change; and,

(iii) The cost-effectiveness of this socio-ecological and systems-based approach to effecting physical activity behaviour change.

## Methods/Design

### The intervention

The Connswater Community Greenway (CCG) [10] is an example of a natural experiment which afforded an opportunity to evaluate the public health impact of a major urban regeneration project in Belfast, Northern Ireland, funded by a £32 million Big Lottery Living Landmarks Award. There are 29 electoral wards in the political constituency of the Greenway with a total population of approximately 110,600, and 22 wards (approximately 87,500 residents) with a geographical centroid within a 1 mile radius. Seven of the wards are within the top 25% most deprived wards in Northern Ireland, as determined by the 2005 Northern Ireland Multiple Deprivation Measure [11]. The aim of the regeneration project is to offer enhanced opportunities for physical activity and outdoor recreation through specific environmental improvements including the construction of 19.4 km of new cycle and walkways and the provision of allotments. In addition, the regeneration aims to improve the aesthetics of shared public spaces, involving the planting of trees/shrubs, erection of public art and the remediation of water courses to improve the natural diversity and reduce the risk of flooding. It is also planned that 24 hour-a-day lighting, CCTV and the presence of park wardens will result in a changed perception of safety in the community. In addition to the range of environmental improvements, a number of interventions to promote physical activity in the CCG area, ranging across the individual, community and environmental dimensions will be implemented. Examples of these interventions include the extension of neighbourhood walking groups and other physical activity initiatives targeted to promote the use of the Greenway in distinct population segments (e.g. young mothers, unemployed and senior citizens), schools-based initiatives and a variety of community-based social marketing initiatives. Theory-based Intervention Mapping will inform the development of the design of these interventions [12], ensuring that physical activity interventions are tailored to meet the needs of the local community [13].

### Overall research design

The PARC Study is a before-and-after evaluation of the effects of the CCG on physical activity and health, and comprises of four main elements:

1. A quasi-experimental before-and-after survey of the CCG population (repeated cross-sectional design), utilising data from a parallel Northern Ireland-wide survey for comparison;

2. Assessment of change in the local built environment and walkability using geographic information systems (GIS);

3. Semi-structured interviews with 60 residents, and a range of community stakeholders before and after the regeneration project;

4. A cost-effectiveness evaluation.

The study has been approved by the Office for Research Ethics Committees, Northern Ireland (09/NIR02/66).

#### Summative evaluation

##### Survey design

A survey of a random selection of households will be conducted before-and-after the regeneration of the CCG. The target area was selected as 29 electoral wards identified during the development of the CCG project (Figure 1). The sampling strategy will ensure proportionality with the Northern Ireland population based on estimates of the number of residents aged 16 or older provided by the 2001 Census. The surveys will each take place over a 12-month period and a random probability sampling framework will be constructed by a random selection of addresses from each of the selected output areas using the Royal Mail’s Postal Address File (PAF), stratified by the proportion of the overall population within each area. An information sheet about the study will be posted to each household, which will be followed up by a visit approximately 1-2 weeks later from a trained interviewer. If no one is present at the time of interview, up to five call-backs will be made in order to achieve a completed interview. If no response to call backs, the address will be recorded and another address within the same area will be selected from the PAF using the same selection process. For each household, the ‘last birthday rule’ (person in the household aged 16 years and over who had the most recent birthday) will be applied to randomly select an individual aged 16 years and over within each selected household to complete the survey. After the individual has given written consent to participate, an interviewer-administered questionnaire will be completed.

**Figure 1 F1:**
[figure not shown]
**The Connswater Community Greenway and PARC Study Sampling Area.** PA=physical activity.

##### Survey outcome measures

The survey content is informed by, and reflects the various levels of, the socio-ecological model comprising measures of individual, community and environmental factors (Figure 2). The primary outcome will be the change in proportion of individuals identified as regularly physically active, according to the current UK recommendations of a minimum of 150 minutes of moderate-intensity physical activity per week [14]. Physical activity will be assessed using the Global Physical Activity Questionnaire (GPAQ) [15]. GPAQ assesses levels of overall physical activity through the accumulation of occupational, transport, and recreational physical activities of moderate and vigorous intensity, and was developed by the World Health Organisation to allow comparison of physical activity across countries.

**Figure 2 F2:**
[figure not shown]
**Overview of the evaluation framework informed by the socio**-**ecological model ****(adapted from Sallis et al 2012 **[51]**).**

Outcomes which may moderate/mediate the relationship between changes in the built environment and physical activity will be assessed. These include (i) perceptions of the characteristics of the environment associated with active travel and physical activity, including aesthetics, safety and walkability [16] - a “walkability index” for each Super Output Area will be created (based on land use characteristics and street connectivity [17,18]) using GIS, to explore the relationship between high and low “walkable” environments and physical activity; (ii) self-rated health using the EQ-5D-3L instrument [19,20]; (iii) health related quality of life using the Short-Form 8 Health Survey (SF-8) [21]; (iv) mental well-being using the Warwick-Edinburgh Mental Well-being Scale [22,23]; (v) common core theoretical constructs such as intention, stage of change, self-efficacy and outcome expectancy based on the outcomes from the 2001 NIH sponsored workshop and studies to develop a unified theory of behaviour change applied to physical activity [24,25]; (vi) items relating to neighbourhood social capital, as reflected in civic engagement, neighbourliness, social networks and support, and perceptions of the local area using the instrument employed in the UK General Household Survey [26,27]; (vii) awareness of the Greenway, assessed using items similar to those employed in an evaluation of the VERB campaign [28] - this will be used to assess the possible mediating effects of social marketing activities to promote physical activity in the CCG area; (viii) individual socio-demographic variables including age, gender, marital status, housing tenure, educational attainment, household income level and employment status. Access to a bicycle and the number of vehicles available for use by the household will also be recorded. In addition, using a tailored questionnaire, a range of discrete choice questions will assess preferences for physical activity with reference to the local built environment, amenities and transport infrastructure [29].

To control for the possible influence of weather patterns on physical activity, data for the seven days preceding interview will be collated from the nearest weather station via the UK MET office. This will include daily rainfall, hours of sunshine, minimum and maximum temperature and wind speed.

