##### Sample size and analyses

The sample size was estimated using the same method as Cochrane et al. [32], based on Cohen’s arcsine transformation [33]. We estimated the initial population proportions of those achieving the recommended levels of physical activity using alternative assumptions of 20%, 30% and 50%. Therefore the sample size required to detect differences in population proportions is 934 at both time points, assuming an effect size of 0.15 at 90% power (α = 0.05). We will survey 950 individuals who reside in the electoral wards whose geographic centroid is within one mile of the CCG area, before and after the intervention. In addition, we will survey a further 289 individuals who reside in other wards in the wider area (representing a similar proportion of the population to the other areas), which will allow us to explore distance decay. Since the “comparator” community survey undertaken by SportNI will involve approximately 4,000 individuals across Northern Ireland, we will essentially have a large control group providing additional power to demonstrate any differences that might emerge in the CCG population.

Area-by-category classifications of change in the proportion of the population meeting the physical activity guidelines will be compared by cross-tabulation and the difference in distributions assessed for statistical significance using the χ^2^ test. Multinomial logistic regression will be used to test a prediction model for categories of change in physical activity by area/age/income bracket, allowing a comparison of odds ratios for the various categories of physical activity by area [34]. A key strength of the analysis will be the capacity to make multiple comparisons between the CCG area and similar groups and areas across Northern Ireland as well as the capacity to analyse trends in physical activity behaviours according to distance between respondents’ homes and the Greenway.

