##### Other data

During the construction of the Greenway, aspects of local or regional transport infrastructure and policy may change, with implications for the active travel behaviour of local residents. Changes will be monitored using routinely available information, including bus timetables and traffic survey data collated by the Department for Regional Development (DRD). The latter will yield comparative information on average annual distances travelled by all forms of transport and access to and use made of public transport. DRD also collects routine information on bicycle use via electronic monitors dispersed throughout the city. In addition, effects on road traffic accidents will be monitored using routinely available statistics, compiled by the Police Service of Northern Ireland (PSNI). The effect of the urban regeneration on tenancy turnover rates, the quality of local social housing stock, and crime statistics in the target area and in neighbouring areas will also be monitored using Northern Ireland Housing Executive and PSNI data respectively.

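### Weather is collected in order to control for it, but neither named analysis includes it, and the unadjusted test leaves the before-after change open to weather and to area-specific changes in who is surveyed

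*Protocol article*

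**What the plan says.** All references are to the protocol article.

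- **Weather (Survey outcome measures).** The purpose is explicit: "To control for the possible influence of weather patterns on physical activity, data for the seven days preceding interview will be collated". The variables are daily rainfall, sunshine hours, minimum and maximum temperature and wind speed, taken from the nearest station.
- **Socio-demographics (same section).** The survey records "individual socio-demographic variables including age, gender, marital status, housing tenure, educational attainment, household income level and employment status". These stand in a list introduced by "Outcomes which may moderate/mediate the relationship between changes in the built environment and physical activity will be assessed".
- **Design (Overall research design).** "A quasi-experimental before-and-after survey of the CCG population (repeated cross-sectional design"), with a parallel Northern Ireland survey for comparison.
- **Test (Sample size and analyses).** Area-by-category classifications of change are to be "compared by cross-tabulation and the difference in distributions assessed for statistical significance using the χ^2^ test".
- **Model (same section).** "Multinomial logistic regression will be used to test a prediction model for categories of change in physical activity by area/age/income bracket".
- **Population turnover (Other data).** "The effect of the urban regeneration on tenancy turnover rates, the quality of local social housing stock" and crime statistics will be monitored from routine sources, in the target area and in neighbouring areas.

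**The concern.** The document announces an adjustment and then names a test and a model that do not make it. A chi-square on a cross-tabulation cannot take account of rainfall or temperature in the week before interview, and the regression terms listed are area, age and income bracket. As written, nothing carries the promised weather control.

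The design makes this matter. Different people are interviewed before and after, so a crude change in the proportion active is the sum of three things: residents changing their behaviour, a change in who lives in or responds from the area, and a change in conditions at the time of interview. The study's aim concerns only the first. Gender, marital status, tenure, education and employment are recorded but appear in neither named analysis. Weather and composition are separate problems: weather varies with time, while composition concerns who is sampled. An unadjusted test is open to both.

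**Working it through.** **1. Stated purpose against stated analysis**

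| Variable | Stated role | In the chi-square? | In the named model? |
|---|---|---|---|
| Seven-day weather | Control | No | No |
| Age, income | Possible moderator or mediator | No | Yes |
| Gender, marital status, tenure, education, employment | Possible moderator or mediator | No | No |

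Only the weather row is a mismatch between what the document says a variable is for and what it does with it. The last row shows which recorded data could be used but are not named.

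**2. The plan's own figure**

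Inputs from Sample size and analyses: h = 0.15, power 90%, α = 0.05.

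n = 2(z₀.₉₇₅ + z₀.₉₀)² / h² = 2(1.960 + 1.282)² / 0.0225 = 933.99, which rounds up to 934. The stated size reproduces with a two-sided test and is not in dispute.

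At a 30% baseline, h = 0.15 corresponds to sin²(arcsin√0.30 + 0.075) − 0.30 = 0.071, or 7.1 points. At 20% and 50% it is 6.3 and 7.5 points.

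**3. Illustration of size (assumed inputs)**

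The document gives no activity gap between groups and no shift in composition. I assume two groups, no behaviour change within either, a stable comparator, 950 Greenway respondents per wave (as planned) and 4,000 comparators per wave (the document says approximately 4,000; I read this as per wave).

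- *Case A:* groups 40% and 25% active; the more active group's share rises from 30% to 40%. Before: 0.3 × 0.40 + 0.7 × 0.25 = 0.295. After: 0.4 × 0.40 + 0.6 × 0.25 = 0.310. Spurious change: 1.5 points.
- *Case B:* groups 45% and 25% active; share rises from 30% to 45%. Before: 0.3 × 0.45 + 0.7 × 0.25 = 0.310. After: 0.45 × 0.45 + 0.55 × 0.25 = 0.340. Spurious change: 3.0 points.

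On the arcsine scale, h = 2arcsin√p₂ − 2arcsin√p₁. Rejection probability = Φ(h/SE − 1.96) + Φ(−h/SE − 1.96).

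| | h | Change in Greenway minus change in comparator, SE = √(2/950 + 2/4000) = 0.0510 | Greenway before-after only, SE = √(2/950) = 0.0459 |
|---|---|---|---|
| Case A | 0.0327 | 0.098 | 0.110 |
| Case B | 0.0641 | 0.241 | 0.287 |

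The nominal rate is 0.05. Case B is 3.0/7.1 = 42% of the effect the study is sized for at a 30% baseline; Case A is 1.5/7.1 = 21%.

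**4. Wider range (assumed)**

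With activity gaps of 10 to 30 points and share shifts of 5 to 15 points, the spurious change (gap × shift) runs from 0.5 to 4.5 points. At a 30% baseline the unadjusted before-after test then rejects with probability 0.06 to 0.56.

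The rejection rates depend only on the size of the differential shift, so they would apply equally to a weather difference of that size. The document offers nothing from which to estimate one.

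**The case against.** The strongest reply is that this is a condensed article. Two sentences on analysis do not claim to list every covariate, and a full list normally belongs in an analysis plan that is not shown. The weather sentence itself shows an intention to adjust. This stands in part: the text does not prove that no adjustment will be made. It is not a full answer, because the article does more than stay silent. It names the test and the model terms, and these do not deliver the control it announces.

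Several safeguards also deserve credit. Both waves use random probability sampling. Each survey runs over 12 months, which balances season. The comparator is contemporaneous, sampled in a similar way, and can be narrowed to similar urban areas, so shifts common to both populations, including regional weather, cancel when changes are compared. Age and income are in the model, and income would absorb part of a socio-economic shift; the illustration ignores that. What remains is any shift specific to the Greenway area, and everything in a Greenway-only before-after contrast.

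Two stronger readings are tempting and should be resisted:

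- A reader might infer that the socio-demographic data were collected to control confounding and then abandoned. The document lists them among possible moderators and mediators; only weather is given a control purpose.
- A reader might infer that the plan expects regeneration to change who lives in the area. Under Other data it says only that effects on tenancy turnover and housing will be monitored. That makes compositional change a possibility, not a prediction.

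Finally, adjusting the primary estimate for everything recorded would carry its own risk. Income, tenure and employment measured after regeneration may be affected by it, and conditioning on them could remove part of the effect.

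**Conclusion.** The point holds in a limited form. The weather control promised under Survey outcome measures is not carried into either analysis under Sample size and analyses, and the named significance test is unadjusted in a design that interviews different people at each wave. Between-year weather differences and area-specific changes in the make-up of respondents can therefore enter the before-after change.

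The size of the bias cannot be computed from the document. If the differential shift were 1.5 to 3.0 points, the controlled contrast would reject about 10% to 24% of the time with no behaviour change. That rests on the assumed gaps and shares above, a stable comparator, 4,000 comparators per wave and no covariate adjustment. Such shifts are under half of the 7.1-point target at a 30% baseline, so the design survives; what is at risk is attributing a modest observed change to behaviour. This should be corrected before the follow-up analysis.

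**What to change.** - **Primary estimate.** Use the wave-by-area term from a logistic model for meeting the activity recommendation, adjusted for age, sex, education and the weather variables already collected. Keep the crude chi-square as supportive.
- **Comparator weather.** Link the same weather data to comparator interviews by date and nearest station, where these are available.
- **Sensitivity analysis 1.** Add income, tenure and employment. They stay out of the primary model because regeneration may change them.
- **Sensitivity analysis 2 (optional).** If the questionnaire records length of residence, repeat the analysis in adults resident since before construction. The questionnaire is not reproduced, so I do not treat the item as missing.
- **Minimum alternative.** If a fuller covariate list already exists elsewhere, one sentence under Sample size and analyses should say that area, age and income are not the whole list and state where weather enters.

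The cost is mainly analysis wording. Covariates must be coded alike in both surveys, and the linkage depends on comparator interview dates and locations, whose availability the document does not state.
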